# Effectiveness of a therapeutic patient education program in improving cancer pain management: EFFADOL, a stepped-wedge randomised controlled trial

**DOI:** 10.1186/s12885-019-5836-5

**Published:** 2019-07-08

**Keywords:** Pain management, Pain cancer, Patient education, Stepped-wedge randomised controlled trial, Quality of life

## Abstract

**Background:**

Despite numerous guidelines, nearly one of two patients with cancer pain remains undertreated, thereby affecting their quality of life. Active patient involvement through Therapeutic Patient Education (TPE) is considered as a relevant strategy to overcoming hurdles in pain management. The aim of the EFFADOL study is to assess the effectiveness of a TPE program in improving cancer pain management.

**Methods/design:**

The EFFADOL study is a stepped-wedge randomised controlled trial. A total of 260 cancer patients with unbalanced background pain will be randomised over the institutional level, i.e. stepped-wedge cluster design. Six clusters will be formed, one at the regional level of “Basse-Normandie” for patients receiving the educational approach by health providers already trained to TPE. Then, five additional centers will be gradually included at the national level, making it possible to compare the “conventional” management of pain (before medical staff training to TPE) with the educational approach (after being trained). The main study parameter is pain interference on daily life assessed with the self-administrated and validated Brief Pain Inventory questionnaire. Secondary objectives comprised the evaluation of patients’ adherence to pain education program, the description of pain intensity, pain relief, analgesic adherence and pain emotional impact. Educational dimension of the program will be evaluated through the patients’ acquisition of knowledge and skills about their pain and treatment as well as their self-efficacy to participate actively in pain management. The patient’s feeling of pain changes will be measured. Finally, the satisfaction of participants and educators will be reported. We hypothetise active involvement of patients in TPE will lead to an improved pain management compared to standard care.

**Discussion:**

Analyzing the impact of a TPE program in cancer pain patients will improve their pain management and quality of life. We expect that the dissemination of our project educational approach through the French territory will be accompanied by long term change in clinical practices with mutual benefit to patients and caregiver-educators.

**Trial registration:**

NCT03297723, registered: 09/28/2017.

Protocol version: Version n°1.1 dated from 2016/09/08.

## Background

Pain remains a prevalent symptom in patients with cancer despite the availability of opioids and current guidelines [1]. Based on a recently updated meta-analysis, pain prevalence is indeed 55% during anticancer treatment [2]. Pain, when it is not effectively treated and relieved, has a severe impact on quality of life [3]. Greco et al. [4] reported that 31.8% of cancer patients still do not receive analgesic treatment proportional to their pain intensity.

The management of cancer pain encounters various obstacles, including patient-related barriers [5, 6] such as the lack of knowledge and representations of patients about pain and its treatment. Barriers include widespread misconceptions about opioid use, underestimation of pain, and non-adherence to treatment [7].

Active patient involvement through Therapeutic Patient Education (TPE) is considered as a relevant strategy to overcoming obstacles in cancer pain management [7]. TPE, as defined by the World Health Organization (WHO, [8]), aims at enabling patients to develop skills to achieve optimal cancer pain control and therefore improve their QoL. TPE programs for pain management have been developed in recent years and the number of published studies evaluating Pain Education Programs (PEP) and establishing the most efficient programs to date has substantially increased, as highlighted in our recent literature review [9]. In particular, Oldenmenger’s systematic review [10] recently performed on 26 Randomised Controlled Trials (RCT) totalling 4735 patients, shows that PEP may result in improvements of relevant patient-reported outcomes. Adam et al. [11] analysed 34 RCT and 8 systematic reviews (including 3 meta-analyses [12–14]) in the field of cancer pain covering nearly 40 years. Reviews showed a slight but statistically significant effect of PEP on knowledge about pain and attitudes towards it, as well as a decrease in pain intensity as reported by patients. Even if there are some evidences of the benefit of PEP on improving pain management, educational interventions are complex. This still raised many issues, including the optimal choice for types of intervention, study designs, and outcome measurements.

In this context and according to the regional health policy, we have undertaken an extensive five-step research program, called EFFADOL (“*Ensemble, Faire FAce à la DOuLeur”*), structured in 5 successive phases, each of them briefly described in the paper developing the EFFADOL combined approach from practice to research [15]. Health professionals were first trained in TPE (step 1). We identified patients’ and relatives’ needs with regard to pain (step 2, [16] prior to design a PEP dedicated on cancer pain (step 3). The PEP evaluation includes an assessment of its feasibility, quality and transferability at the regional level (step 4) and of its effectiveness at the French level through an interventional comparative randomisation (step 5).

Thus, the research steps (2, 4, and 5) complement the implementation of the PEP (Step 3) answering to the ethical and regulatory requirements of TPE that place emphasis on the importance given upstream to the identification of patient expectations and needs (Step 2,) and downstream on that of evaluation (Steps 4 and 5). The proposed strategy, beyond these requirements, confers a prospective experimental dimension to the whole project in order to answer the following research question: does TPE allow patients suffering from cancer to manage their pain better on a daily basis? We herein detail the methodology of the evaluation step 5 aiming to evaluate the effectiveness of our PEP in improving pain management among cancer patients.

### Objectives

The main objective of this study (Step 5 of the EFFADOL program) is to assess the PEP effectiveness on patients’ pain through pain interference with daily life as main judgement criterion.

We will further evaluate the proportion of patients adhering to the whole PEP at the Basse-Normandie scale (Step 4), and then at the national level after medical staff being trained to TPE.

Other secondary objectives, dealing with the overall effect of pain education on pain management, aim:

- To assess pain intensity, pain relief, and emotional impact.

- To assess patients’ skills and knowledge.

- To evaluate patients’ participation, satisfaction, and impression of change.

## Methods/design

### Study design

The impact and benefit of the PEP will be evaluated by comparing the educational approach and the “conventional” management of pain. The Step 5 of the EFFADOL project is a multicentre, stepped-wedge, cluster randomised controlled trial. This particular randomised design known as the step-wedge procedure [17–19] minimize the risk of contamination between the two groups (conventional vs TPE approach) and thereby the risk of bias. Indeed, when the purpose is to compare two practices (in this case, TPE and conventional care) in which the attitudes of the caregivers are changed, it is critical to set up at the same time, and with the same health staff the two assessed different modes of care. The stepped-wedge design particularly suits in such setting since it makes it possible to stagger the training of the caregivers hospital by hospital and consequently that of the educational intervention per participating centre. The randomisation is performed at the cluster level, instead of the patient level.

Thus, 6 clusters will be formed in which TPE dispensing will be strictly identical. The first cluster includes 11 participating centres from Basse-Normandie where enrolled patients will all receive the educational approach as healthcare (physician/nurse) staff at the regional level have been already trained in TPE (Step 1 of the EFFADOL project). Then, five other clusters that correspond to five participating centres outside the region at the national level will be gradually included in a stepped-wedge design (Fig. 1). Finally, the conventional approach (before training) will be compared to the educational approach (after being trained).

**Fig. 1 Fig1:**
[figure not shown]
Schematic representation of the stepped-wedge design

### Study population

Eligibility criteria are detailed in Table 1. More specifically, pain-related criteria are based on the definition of unbalanced background pain according to the Standards, Options and Recommendations [20]. Briefly, the targeted patients had to experience pain related to disease or its treatments, pain during the previous week, pain intensity greater or equal to 4 on a scale of 10, or pain stopping them from sleeping, or more than 4 episodes of paroxysmal pain per day, or an impact or their daily activities.

**Table 1 Tab1:** Study eligibility criteria

Inclusion criteria	- Patient suffering from a cancer diagnosed since at least 1 month - Pain related to the pathology or its treatment and/or to the sequelae of disease and its treatment (ongoing or not): - treated with analgesics since at least 1 month - moderate to severe intensity, unbalanced, in the previous week: • Pain intensity ≥4 (on a 0–10 numerical rating scale) • OR leading to insomnia • OR > 4 daily breakthrough pain • OR interference with daily activities - Patient with a life expectancy ≥6 months - Health compatible with the PEP requirements (WHO performance scale ≤2) - Patient with a signed informed consent before inclusion of the study - Patient ≥18 years old - Patient able to understand, speak and read French - Patient without cognitive dysfunctions
Exclusion criteria	- Primary central nervous system cancer or brain metastases - Documented cognitive disorders - Progressive psychiatric disease - Drug user - Heavy drinking, superior to the WHO recommendations - Patient refusal to participate

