#### Primary and secondary endpoints

The main judgement criterion in this study is the impact of pain on daily activities measured with the BPI. A score will be established by averaging the response on the 7 items of the subscale 9. The benefit of TPE on the impact of pain will be defined as a 2-point-decrease (on a scale of 10) between the values measured before and at the end of the PEP (at 8 weeks after inclusion). A 2-point decrease on the BPI scale correspond to a clinically significant improvement [32].

The first secondary endpoint is the proportion of patients adhering to the whole PEP (3 sessions), adherence being defined as the achievement of these 3 sessions for patients who undertook to follow them.

Other secondary endpoints are based on:

- Pain intensity and relief (BPI), its impact on QoL (subscale 9 of BPI, HADS), qualitative characteristics of pain (QDSA) and pain adherence.

- Patient’s knowledge and skills about pain, patient’s self-efficacy to actively manage pain, patient-reported impression of improvement.

- Participants’ satisfaction and educators’ satisfaction with PEP.

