#### Data analysis

At every stage of the analysis, exploratory data will provide, for quantitative variables, mean, its standard deviation, median, quartiles, and missing data; for qualitative variables, frequencies and 95% confidence interval. Statistical tests and confidence intervals will be calculated with an overall error significance level of 5%. For the main objective (Step 5), statistical analysis will be done on the per-protocol population: it will concern assessable patients who have completed the whole program (3 sessions after the educational diagnosis).

Pain interference with daily life scores at 8 weeks post inclusion will be first compared between experimental PEP group and control group, in consideration of the correlation of data (generalized linear mixed model).

For the first secondary objective (Step 4), patients’ adherence to the PEP at the regional scale will be assessed using one-sided test comparing a proportion to a reference value.

For all the steps, a global analysis will be performed, taking into account the different periods of the study, clusters, and the care provided for each period, using a generalized linear mixed model for scales scores and for qualitative results obtained from questionnaires. This analysis will be adjusted to the patients’ demographic and clinical characteristics.

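### Patients are recruited individually after the centre's phase is known and agree to different burdens by phase; Table 1 levels health but not willingness or ability to attend, so the comparison is open to recruitment bias.

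*Protocol article*

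**What the plan says.** The Study design section of the protocol article states: "The randomisation is performed at the cluster level, instead of the patient level". It defines the contrast by staff training: "the conventional approach (before training) will be compared to the educational approach (after being trained". In the Basse-Normandie cluster there is no control phase: "enrolled patients will all receive the educational approach as healthcare (physician/nurse) staff at the regional level have been already trained in TPE".

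Patients enter one at a time. Table 1 (Study population) requires "Patient with a signed informed consent before inclusion of the study" and lists "Patient refusal to participate" among the exclusions. On fitness for the programme it requires "Health compatible with the PEP requirements (WHO performance scale ≤2". Table 1 is a single list and does not distinguish the phases.

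The Study flowchart section gives every participant assessments at baseline and at 8 weeks, and gives PEP patients two further assessments during the programme. The footnotes to Table 2 allow questionnaires to be completed at a hospital visit or by post, and have the control patients' questionnaires sent 8 weeks after inclusion. The programme itself is an educational diagnosis followed by three sessions (Data analysis). An undertaking to attend is mentioned in one place, the first secondary endpoint: "adherence being defined as the achievement of these 3 sessions for patients who undertook to follow them".

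**The concern.** Randomising clusters balances patients only if the way individuals enter does not depend on the phase. Here staff who know whether they have been trained identify and approach the patients, and the patients are asked to join something different in each phase. Someone who would return two sets of questionnaires but would not, or could not, attend three sessions can enter as a control and may decline in the PEP phase. The two groups could then differ in motivation, mobility or severity from the first day.

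This is separate from the completer rule in Data analysis ("it will concern assessable patients who have completed the whole program (3 sessions after the educational diagnosis"), which acts after inclusion. Replacing that rule with an intention-to-treat analysis would leave the entry problem where it is. At stake is whether a difference in 8-week interference reflects the programme or who agreed to join.

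**Working it through.** **Step 1: entry conditions by phase.**

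| | Control phase | PEP phase | Source |
|---|---|---|---|
| Staff know the phase | yes, not yet trained | yes, trained | Study design |
| Individual consent; refusal excludes | yes | yes | Table 1 |
| Health (WHO performance status 2 or better) | required | required | Table 1 |
| Willing and able to attend three sessions | not asked | not an entry criterion, but an undertaking is implied | Table 1; Primary and secondary endpoints |
| What the patient joins | baseline and 8-week questionnaires | the same, plus educational diagnosis, three sessions and two further assessments | Study flowchart; Table 2 footnotes; Data analysis |

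The health row is level. The willingness row is not.

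**Step 2: the plan's own sample size.** Inputs from Sample size calculation: difference 2 points, SD 2.5, ICC 0.05, 3 clusters per arm, two-sided 5%, power 80%.
- Independent patients: 2 × [2.5 × (1.960 + 0.842) / 2]² = 24.5, so 25 per arm; 26 with the t distribution.
- Design effect with 15 per cluster: 1 + (15 − 1) × 0.05 = 1.70.
- 25 × 1.70 = 42.5 (43); 26 × 1.70 = 44.2 (45). The stated 45 per arm is reproduced.
- Standard error of the difference at 45 per arm: 2.5 × √(2 × 1.70 / 45) = 0.687. Like the plan's calculation, this treats the design as parallel clusters. Power for 2 points is then about 83% (normal approximation).

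**Step 3: what an entry shift would do.** Let b be the difference in mean 8-week score caused by selection alone. The documents give no value for b, so the values below are assumptions.
- If there is no programme effect, the two-sided error is Φ(−1.96 + b/SE) + Φ(−1.96 − b/SE).
- If the true effect is 2 points and selection works against the programme, power is Φ((2 − b)/SE − 1.96).

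| Assumed b (points) | Error, 45 per arm | Error, 75 per arm | Power if selection works against PEP, 45 per arm |
|---|---|---|---|
| 0.25 | 6.5% | 7.6% | 72% |
| 0.5 | 11% | 16% | 59% |
| 0.75 | 19% | 29% | 44% |
| 1.0 | 31% | 47% | 31% |

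The column for 75 per arm (SE = 2.5 × √(2 × 1.70 / 75) = 0.532) uses the planned 5 × 15 = 75 controls and assumes as many PEP patients. The error is larger there because more patients shrink the SE but not the bias.

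**Step 4: what such a shift requires.** If a share s of controls would have declined the sessions, and their mean score differs by d points from that of the other controls, then b = s × d. Taking d = 2 points, borrowed from the target difference only as a scale, b = 0.25 needs s = 0.25/2 = 12.5%, b = 0.5 needs 25% and b = 1.0 needs 50%. The top of the range is therefore demanding. Neither s nor d is in the documents.

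**The case against.** The strongest reply is that this is a general hazard of cluster trials with individual consent, and that the text does not show it happening here. Much of that stands.

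- A reader might infer that PEP patients must commit to three sessions in order to enter. Table 1 contains no such criterion. The undertaking appears only in the definition of the adherence endpoint.
- The performance-status criterion applies to controls too. It works against a fitness imbalance and is not evidence of different selection.
- A reader might infer that the bias favours the programme. Patients with worse interference may be the more willing to accept education, so the direction is open.
- A reader might infer that training changes how staff judge eligible pain. Table 1 gives explicit alternatives that rest largely on patient report, and although the interference alternative has no threshold, nothing says that training alters its use.
- The proportions 0.70 and 0.85 in Sample size calculation might look like a guide to refusal. They concern completion of the whole programme and do not estimate refusal at entry.
- There is partial protection. All participants have a baseline assessment, benefit is defined as a decrease from the value before the programme, and the global mixed model takes account of period and cluster and adjusts for demographic and clinical characteristics.
- Screening logs, baseline tables by phase and full covariate lists may sit in the full protocol or SAP. Their absence from an article is not a fault.

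What the reply does not answer is the eligibility list itself. Table 1 is stated, covers both phases and leaves willingness and ability to attend unlevelled. Later analysis cannot fully repair that. The comparison stated first in Data analysis is of 8-week scores allowing for correlation; adjustment is mentioned only for the global analysis, without naming baseline BPI.

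**Conclusion.** The point holds as a risk, not as a demonstrated bias. Staff know the phase, patients consent individually to different burdens, and Table 1 equalises health but not readiness to attend. That patients also know the phase is an inference, though someone asked to attend three sessions would know it.

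Size and direction are unknown. The error rates of about 6.5% to 31% rest entirely on assumed shifts of 0.25 to 1.0 points and on the plan's SD, ICC and 45 per arm. They show what would matter, not what will occur. The documents do not support saying that the groups are selected differently, that the result is biased, or that it is biased towards the programme. Safeguards in material not shown cannot be excluded. This is an inexpensive improvement to the design, and one best made before inclusion.

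**What to change.** Add one inclusion criterion to Table 1 for both phases: willing and able to attend three education sessions over the next 8 weeks if offered, confirmed before inclusion. In addition, adjust the primary 8-week comparison for baseline BPI interference. This needs no new data, since all participants are assessed at baseline and the primary endpoint already relies on a value from before the programme.

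The costs are:
- Some control candidates are lost. The documents do not give the number. If a share s would say no, each of the five centres needs 15 / (1 − s) otherwise eligible candidates to reach its 15 controls; with s = 25%, an assumption, that is 15 / 0.75 = 20.
- Controls learn that a programme exists, in a design chosen partly to limit contamination. The question should therefore be worded neutrally and should not describe the content of the sessions.
- Stated willingness is not attendance, and baseline adjustment reduces but does not remove bias from unmeasured motivation. The criterion also does not deal with any difference in how staff identify patients.

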### Study flowchart

For all the participants with signed consent form, assessments will be conducted at baseline and 8 weeks after inclusion (Fig. 2). For patients of the experimental PEP group, complementary assessments will be performed twice during the program.

**Fig. 2 Fig2:**
[figure not shown]
Study flowchart. Abbreviations: PEP Pain Education Program

### Assessments

Validated questionnaires and scales used for assessments are presented in Table 2. At inclusion, previous medical history will be reported as well as relevant indications (cancer and pain data, analgesic treatment…).

**Table 2 Tab2:**
[figure not shown]
Questionnaires and scales used to assess pain, educational impact and satisfaction with the PEP

^1^ Questionnaires will be filled during a visit to hospital or sent by post

^2^ At inclusion

^3^ For control patients, questionnaires will be addressed 8 weeks after inclusion

*Abbreviations: PEP* Pain Education Program

#### Assessment of pain and its impact, and evaluation of analgesic treatment adherence

The “Questionnaire concis sur les douleurs”, corresponding to the validated French translation of the Brief Pain Inventory (BPI, [21, 22]), is very commonly used in research protocols [9]. It allows a rapid self-assessment of the impact of pain on daily activities, using 7 items (general activity, mood, walking ability, normal work, relations with other people, sleep, and enjoyment of life). The use of subscale 9 is therefore recommended by the French National Authority for Health (HAS) to assess QoL in patients suffering from pain [23]. The BPI will be also used to calculate the Pain Management Index (PMI), which, combining intensity and analgesic treatment, can assess the proper use of analgesics [24]. Moreover, adherence to analgesic drugs will be assessed with a pain-adapted questionnaire.

Among the other criteria (assessed only in PEP group), emotional repercussions will be assessed by the Hospital Anxiety and Depression Scale (HADS, [25] and the qualitative assessment of pain will be measured by the short form of the McGill Pain Questionnaire [26] in its French version (Questionnaire de Saint-Antoine (QDSA), [27]).

